### Trial design {8}

EMBRACE is a randomized, placebo-controlled, delayed-start trial that investigates neuroimaging, blood biomarkers, and clinical changes associated with psilocybin therapy in those with a unipolar depressive disorder. The protocol is documented as adhering to the SPIRIT checklist [see Additional file 1]. For the purposes of this study, a depressive disorder will include MDD or persistent depressive disorder (PDD) as indicated by the Mini-International Neuropsychiatric Interview (MINI) with a current major depressive episode as defined by the DSM-5.0 and confirmed by an interventional psychiatrist [75]. Study assessments/visits will occur at intervals that are reported in Fig. 2. This study aims to recruit and treat up to 50 participants at Sunnybrook Health Sciences Centre, University of Toronto, Toronto, Ontario, Canada. Participants will be screened by a study coordinator to determine study eligibility, and if eligible will undergo a baseline assessment, preparatory supportive psychotherapy, and neuroimaging 1 week prior to randomization. At the first treatment session (Treatment Visit 1), participants will be randomized to either group 1 or group 2. Participants in group 1 will receive a high dose of synthetic psilocybin (25 mg) while in group 2 will receive inert placebo (25 mg MCC). Three weeks later (Treatment Visit 2), participants in group 1 and group 2 will both receive a high dose of synthetic psilocybin (25 mg). This delayed-start design allows for the comparison of outcomes between the two groups while also evaluating the effect of the intervention over time. At each Treatment Visit, all participants will undergo neuroimaging after dosing, and two qualified staff members will observe and provide supportive psychotherapeutic support for approximately 8 h post-treatment administration. A diagram of the study design and stages is presented in Fig. 1.

**Fig. 1 Fig1:**
[figure not shown]
Study design

## Methods: participants, interventions and outcomes

### Study setting {9}

The study population will be recruited from the Harquail Centre for Neuromodulation, Mood & Anxiety Disorders Programs and general psychiatry clinics at Sunnybrook Health Sciences Centre, University of Toronto, Toronto, Ontario, Canada.

### Eligibility criteria {10}

Fifty participants (> 18 and < 65 years) will be recruited. Potential study participants will have been referred by their circle of care and will undergo pre-screening and confirmation of diagnosis by the study Qualified Investigator (QI), who is an interventional psychiatrist, prior to enrolment in the study. During this assessment, a thorough medical, psychiatric, and medication history assessment will be performed by the QI. Participants will need to have a MINI-confirmed diagnosis of a depressive disorder and meet criteria for a current major depressive episode (MDE) as defined by the DSM-5, which will be confirmed by the QI. Depressive symptoms must be in the moderate-to-severe range at the time of enrolment, as measured by the 17-item Hamilton Rating Scale for Depression (HAMD-17). A 12-lead ECG recording will be obtained to monitor for QTc prolongation and other conditions. Detailed recommendations will be provided for a medication(s) tapering schedule(s) if a participant is taking one or more psychotropic medications prior to study enrolment. Careful monitoring of the participant during a tapering period (~ 2–5 weeks based on tolerability) and during the subsequent 2-week washout period will be done by a study psychiatrist in collaboration with the participant, their primary caregiver, as well as their primary care provider to ensure appropriate down-titration and washout. A washout period will be mandatory if a participant is taking a prescribed antidepressant medication (e.g., SSRIs/SNRIs, tricyclic antidepressants, lithium, MAOIs) and must be undertaken before the trial start date. SSRIs/SNRIs (except fluoxetine), tricyclic antidepressants, antipsychotics, lithium, and monoamine oxidase inhibitors (MAOIs) must be tapered under the direction and supervision of the QI for 2–4 weeks (SSRIs/SNRIs/TCAs), 2–4 weeks (antipsychotics), 4 weeks (Lithium), and 5 weeks (MAOIs and fluoxetine), respectively, and then discontinued prior to receiving the first dose of psilocybin/placebo. The QI will provide detailed instructions to participants for tapering psychotropic medications and will monitor the participant during both the taper and wash out period, prior to the initial dose of psilocybin/placebo [see Additional file 2]. The individualized dosage reduction plan will be developed in collaboration between the QI and the participant, their primary caregiver, and their primary healthcare provider.

Participant enrolment will begin after the screening and tapering period of any medications, but prior to their 2-week washout period. Confirmed enrolment will then trigger randomized allocation of participants to either Treatment Group. Any woman capable of becoming pregnant (e.g., had a menstrual period within the last 12 months) will have their blood analyzed for a βHCG level to rule out pregnancy prior to participating in the study. They will also be required to complete a urine pregnancy test on each treatment day before each treatment administration, and will be counseled to use effective contraception if sexually active during the treatment period.

### Who will take informed consent? {26a}

The study coordinator will have completed all regulatory training in compliance and as mandated by Health Canada and Sunnybrook Research Institute, and the study coordinator will obtain written informed consent from each person that participates in the study. Enrolment will continue until the target sample is reached. Participants will be informed of the background, purpose, procedures, and potential risks or harms associated with the study. It will be expressed to the participant that their participation in the study may be withdrawn at any point during the study without penalty or repercussion.

### Additional consent provisions for collection and use of participant data and biological specimens {26b}

The exploratory aim examines whether blood biomarkers will be associated with treatment responses and thus the informed consent for this study describes the blood draw as an optional data collection. Furthermore, biofluid data collection could be used as part of future studies.

## Interventions

### Explanation for the choice of comparators {6b}

In this randomized, single-center, delayed-start neuroimaging clinical trial, participants will be randomized to receive a high dose of psilocybin (25 mg PO) or MCC (25 mg) in a double-blind manner at the first of two treatment visits. MCC was chosen as the inert placebo as it reduces the potential side effect burden on participants and has no direct effects on cerebrovascular function relative to an active placebo. This choice of placebo will generate positive drug effect expectations during core neuroimaging assessments and has been widely used in many placebo-controlled trials involving psilocybin [22, 27, 76–78].

Three weeks later, all participants, regardless of randomization, will receive psilocybin 25 mg PO. Several phase I and II trials report high dose (25 mg) of psilocybin as having a robust antidepressant effect [23, 79]. The psilocybin dose for this study is reported to be unaffected by age and body mass with respect to total drug exposure and maximum plasma concentration [80] and was comparable to the selective serotonin reuptake inhibitor (SSRI) escitalopram in terms of both efficacy and adverse event frequency [22]. For this study, synthetic psilocybin (25 mg) and inert MCC placebo (25 mg) will be provided by the medical research organization Usona Institute. Both psilocybin and MCC capsules will be individually pre-packaged into high-density polyethylene bottles (25 cc) and labelled with randomized codes in a double-blind manner. MCC is United States Pharmacopeia (USP)-grade encapsulate.

### Intervention description {11a}

There will be a total of two treatment visits on-site at Sunnybrook Health Sciences Centre. For the first treatment visit on day 14, half of the participants (experimental arm) will be administered one 25 mg capsule of psilocybin taken orally with water, while the other half (control arm) will be administered one 25 mg MCC capsule taken orally with water. Three weeks later, all participants will receive one 25 mg capsule of psilocybin taken orally with water during their second treatment visit as a delayed-start measure. Supportive psychotherapy will be provided in conjunction with the consumption of both psilocybin and placebo by two registered psychotherapists licensed by a recognized regulatory body in Ontario (e.g., College of Registered Psychotherapists of Ontario)**.** This therapy will encompass practical support, relaxation techniques, and integration techniques, fostering participants’ openness and curiosity about their experiences. Additionally, unlicensed psychotherapists undergoing licensure may participate in the trial under the direct supervision of a licensed psychotherapist. Following administration of each treatment and their subsequent MRI scan, participants will be guided to a recovery room—a carefully curated therapeutic physical environment that is both esthetically pleasing and conducive to safety—to resume their psychotherapeutic support for the duration of their psychedelic experience until effects have subsided (around 6–8 h post-ingestion). To enhance participants’ positive subjective experiences, the recovery room will have comfortable furniture and soft lighting and resemble a home-like ambiance. Preparatory psychotherapy sessions will be provided beforehand to familiarize participants with the clinical settings, including the recovery room and the route to the MRI scanner. During these sessions, participants will be guided through the procedures that will take place during the study while establishing comfortability, trust, and a positive rapport with the study team.

### Criteria for discontinuing or modifying allocated interventions {11b}

According to the terms of participant safety and voluntary withdrawal, participants who request withdrawal from the study at any time will be immediately withdrawn with no further data collected and the cessation of intervention administration. Participants will not be required to provide reasoning for their withdrawal of consent. However, if reasoning for study withdrawal is voluntarily provided, this will be recorded along with survival data up to the protocol-described follow-up period. Any data collected prior to the withdrawal of consent may be retained and used by Sunnybrook Research Institute. Research staff may also withdraw participants if they are rendered unable to tolerate the trial medication, whether there is a serious adverse event or a persistent adverse event that impedes their daily functioning. The withdrawal procedure also extends to those who are unable or unwilling to follow the study procedures, those who are diagnosed with any medical condition that, in the Qualified Investigators’ opinion, may jeopardize their safety if they were to continue in the trial. If the participant plans to or becomes pregnant during the trial, the QI may stop a participant’s involvement in the study without their consent. If the Sponsor decides to stop the study or if the Regulatory Authority(ies)/research ethics board withdraws permission for the study to continue, the immediate cessation of involvement for all participants will be done without their consent.

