The neurobiological mechanisms underpinning psilocybin’s antidepressant response remain unclear but likely involve changes in neuroplasticity at both cellular [36, 37] and connectomic level [37–39]. In this context, *neuroplasticity* refers to the brain’s ability to adapt structurally and functionally in response to psilocybin [40–42]. Previous research in MDD suggests increased dynamic functional activity and neural flexibility measured by BOLD-fMRI and magnetic resonance spectroscopy [43] during the subacute treatment phase (days to weeks post-dosing). However, the acute effects (e.g., < 24 h post-dosing) of psilocybin-evoked neuroplasticity in MDD remain unknown. Moreover, psilocybin’s agonism at serotonin 5-hydroxytryptamine (5-HT) receptors and its role as a glutamatergic agent are implicated in its neuroplastic mechanisms [44–47] and psychological phenomena such as ego dissolution (i.e., the subjective experience of a breakdown in one’s sense of self and separation between oneself and the world) [43, 48, 49], dream state-like cognitive processing [12, 49], and putative molecular antidepressant mechanisms [36, 50–52].

Placebo effects are well-documented in conventional antidepressant trials in the absence of acute treatment effects [53, 54]. Spontaneous remission of untreated MDD symptoms can occur for many reasons but may take longer compared to antidepressant treatments [55–57]. A recent phase 2 trial comparing psilocybin to an active placebo alongside supportive psychotherapy found significant benefits of psilocybin over placebo on Montgomery-Åsberg Depression Rating Scale (MADRS) and Sheehan Disability Score measures up to 6 weeks post-treatment [58]. However, no difference in MADRS was found at 2 days post-treatment, suggesting psilocybin’s neurobiological effects occur before symptom improvement. This underscores the need to investigate acute brain network changes during psilocybin treatment versus placebo to better understand how psilocybin immediately alters functional connectivity and the neurophysiological mechanisms linked to mood changes in MDD. This exploration may aid in identifying early treatment response markers [54]. For this study, the “acute” timeline will denote any changes that manifest on the day of psilocybin treatment, whereas the “subacute” timeline will encompass any change that occur during the subsequent weeks of follow-up.

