### Provisions for post-trial care {30}

Follow-up assessments will be required after each treatment visit to provide additional psychotherapeutic support and to allow for participant reflection. Participants who have discontinued or completed their participation in the trial will be permitted to resume their usual standard-of-care for their depression symptoms. Participants will be advised in the informed consent that they will need completed paperwork by their general practitioner or psychiatrist to apply to Health Canada’s Special Access Program for compassionate care if they express interest in continuing psilocybin treatment for their depression symptoms beyond the study’s duration. They will also be informed that neither granted access nor affordability can be guaranteed if they pursue this option.

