**Fig. 2 Fig2:**
[figure not shown]
Schedule of events

A week into each participant’s washout period, a baseline assessment (day 7) will be conducted, which will include clinical scales, a baseline MRI, and an optional blood biomarker collection, if the participant has indicated their agreement to provide this on the written consent form. One week (day 14) after baseline is the first treatment visit where clinical questionnaires will be completed. Afterwards, participants will be administered either 25 mg of psilocybin or MCC placebo depending on their randomized group allocation. Over the course of 8 h post-psilocybin intake, participants will be monitored every 30 min for routine vitals (HR, BP, %SPO_2_) and dissociative symptoms, using the 6-Item Clinician Administered Dissociative Symptoms Scale and mental status examination by the study coordinator. Approximately 1 h after dosing, participants will undergo a second MRI scan that will include a T1-weighted anatomical scan, ASL and resting-state fMRI sequence with the total scan time lasting approximately 1 h. Participants will then be brought by study personnel to a comfortable room where supportive psychotherapy will be provided. An ECG will be performed within 48 h after treatment administration on the first treatment day. All participants will have a follow-up visit 1 day after the initial treatment that includes relevant clinical scales, psychotherapeutic support, and participant reflection. A second follow-up visit 1 week after the first treatment visit will be remote and will include relevant clinical scales, psychotherapeutic support, and participant reflection. Participants will return to the hospital for open-label treatment with psilocybin 25 mg on the second treatment visit. The QI or delegate will be in-house and available on-call during this time to manage any emergency situations should they arise. Supportive psychotherapy will be provided by a study psychotherapist during each participant’s psilocybin or placebo treatment. Prior to participant discharge, a risk assessment will be performed to ensure that they are safe to leave the center (e.g., risk of harm to self or others and likely serious physical impairment due to their mental state). If they are not deemed safe to leave by study personnel, the QI or delegate will be promptly notified, and the participant will be offered additional time for recovery. If the time exceeds the normal working day, the study QI/delegate will remain available to monitor the participant until the participant’s risk level is reduced and is suitable for discharge home or, if necessary, bring the participant to the emergency department and/or admit directly to the psychiatric unit for further emergency psychiatric care and stabilization.

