## Assignment of interventions: allocation

### Sequence generation {16a}

Participants will be randomized with a computer-generated 1:1 randomized allocation into either the psilocybin or placebo group for dosing visit 1 by an independent external assistant using REDCap Randomization Module. Each participant will have an equal probability of being added to either group. Group sizes will be fixed, and study personnel will be blind to randomized allocation. A flowchart for participant randomization is provided [see Additional file 5]. All participants will receive open-label psilocybin at the second treatment visit.

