## Data collection and management

### Plans for assessment and collection of outcomes {18a}

The assessments to be collected for both primary and secondary outcomes can be found in Table 2. For each participant, much of the data will be securely stored in the form of an electronic case report form (eCRF) which will include participant demographics, clinical scales and assessments, medical information including any pre-existing conditions and history, concomitant medications and therapies, vital signs (i.e., ECG, blood pressure), baseline blood tests, follow-up visits, any AEs or SAEs (if applicable), documentation of a participant’s informed consent, study visit dates, participant identification numbers, and any documentation pertaining to the appropriate data entry, management, validation, and archival. Paper-based copies of study questionnaires will be kept in the physical CRF with the unique, anonymized identification number assigned to a given participant and securely stored on-site in an area with restricted access at the hospital. Participant data captured during the trial will only be identified by a participant ID and managed in the electronic CRF (eCRF) that will be securely stored in online Research Electronic Data Capture (REDCap) software. REDCap is a secure, web-based software that is designed to support data capture for clinical trials and research studies. MRI data will be stored on a secure research server at Sunnybrook Health Sciences Centre. All questionnaires used in the study have been previously published and validated for research and/or clinical use. The ASL and MRI techniques have been previously published and validated.

**Table 2 Tab2:** Primary and secondary outcomes

**Primary outcomes**	• Significant alterations in regional CBF across three a priori brain regions from baseline to treatment visit 1
	• Improvement in depressive symptoms using the Montgomery-Asberg Depression Rating Scale (MADRS) from baseline to week 3 and week 6 following initial psilocybin/placebo administration. Higher scores with respect to the MADRS minimum (0) and maximum (60) values represent a worse treatment outcome [89]

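### The stated withdrawal procedure ends data collection as well as dosing and is extended to some participants who have not withdrawn consent, so a few obtainable week-3 MADRS scores could be lost

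*Protocol article*

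**What the plan says.** Section {11b} of the protocol article gives several routes out of the trial.

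- **At the participant's own request:** "participants who request withdrawal from the study at any time will be immediately withdrawn with no further data collected and the cessation of intervention administration". A reason, if volunteered, is recorded together with survival data.
- **Intolerance or adverse event:** "Research staff may also withdraw participants if they are rendered unable to tolerate the trial medication". Nothing is said about data collection afterwards.
- **Non-compliance or a new medical condition:** "The withdrawal procedure also extends to those who are unable or unwilling to follow the study procedures". The same sentence covers people whose newly diagnosed condition makes continuing unsafe in the QI's opinion.
- **Pregnancy:** the QI may end the person's involvement without their agreement. Data are not mentioned.

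No sentence provides for stopping study drug while staying in outcome follow-up.

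Three other places bear on this:

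- Table 2 lists MADRS improvement as a primary outcome, "from baseline to week 3 and week 6 following initial psilocybin/placebo administration". The Objectives section {7} treats the MADRS comparison as a secondary objective.
- The sequence generation section {16a} states: "All participants will receive open-label psilocybin at the second treatment visit".
- The missing-data section {20c} says that, for dropouts after the first dose, the last observation enters an intention-to-treat analysis.

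**The concern.** Stopping a drug and leaving a study are different events, and only withdrawal of consent requires that data collection stop. Here the one procedure that is spelled out joins the two, and it is then applied to people who may be willing to go on being assessed.

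The design makes this loss needless. The arms differ by one supervised capsule at Visit 1, and the next capsule is open-label psilocybin for everyone. A participant removed after Visit 1 has had the complete randomised treatment. Omitting the second capsule deals with any risk from further drug, and ending MADRS assessment adds no protection.

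What is at stake is the week-3 MADRS, the listed MADRS time point that still compares psilocybin with placebo. Week-3 remission, a secondary outcome in Table 2, rests on the same score. An intention-to-treat analysis is weakened if scores that could have been obtained are not collected.

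**Working it through.** **1. Which routes end data collection?**

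| Route in {11b} | What the text says about data | Reading |
|---|---|---|
| Requested withdrawal | Collection ends | Explicit, and proper |
| Non-compliance; new medical condition | The withdrawal procedure is extended to these cases | Collection ends, on the most natural reading |
| Intolerance or adverse event | Nothing | Unclear |
| Pregnancy | Nothing | Unclear |

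The only procedure set out before the extending sentence is the one for requested withdrawal, so that is what appears to be extended.

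**2. Who can lose a week-3 score?** Visit 2 is three weeks after Visit 1, so week 3 falls at Visit 2, day 21 after the first dose. Removal after that point can affect only week 6, by which time both arms have been scheduled to receive psilocybin. The exposed group is therefore those removed between Visit 1 and the week-3 visit without withdrawing consent. Randomised doses still to come for them: 1 − 1 = 0.

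**3. What would be used in place of the missing score?** The timeline section {13} gives contacts at 1 day and at 1 week after Visit 1.

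- From the 1-week contact to week 3: 21 − 7 = 14 days, or 14/21 = 67% of the interval.
- From the 1-day contact: 21 − 1 = 20 days, or 20/21 = 95%.

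These are calendar gaps and do not measure bias. The schedule figure is not shown. If MADRS is not taken at those contacts, the last score precedes the dose. Whether section {20c} means carrying a value forward or simply keeping the data up to dropout in the mixed model, the actual week-3 score is absent. The Background {6a} reports that in one phase 2 trial "no difference in MADRS was found at 2 days post-treatment", although benefit was seen up to 6 weeks. That is a reason not to let a 1-day score stand in for week 3. It says nothing about a 1-week score.

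**4. How large is it?** Each participant affected is 1/25 = 4% of an arm. The article gives no removal rate, MADRS difference or MADRS SD, and no MADRS power calculation. The following range is therefore illustrative only. It assumes a two-sided 5% test, equal loss in both arms, and lost participants contributing nothing:

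power = Φ(Δ / (SD × √(2/n)) − 1.96)

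| Assumed loss | n per arm | Δ = 8, SD = 10 | Δ = 6, SD = 10 |
|---|---|---|---|
| 0% | 25 | 80.7% | 56.4% |
| 5% | 23.75 | 78.7% | 54.3% |
| 10% | 22.5 | 76.5% | 52.1% |
| 20% | 20 | 71.6% | 47.5% |

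**5. Is the plan's own sample-size figure touched?** No. The article's only computed size is 20 per group for more than 80% power on the CBF contrast. Simulation from its stated inputs (random-intercept mixed model, three visits, age and sex omitted because their effects are not given, Sidak level 1 − 0.95^(1/3) = 0.01695, 200 datasets per size) gives 61.5% at 15 per group, 81.5% at 20 and 88.5% at 25, which agrees. The Visit 1 scan takes place about 1 hour after dosing, so later removal cannot affect it.

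**The case against.** The best case against is that the point rests on one ambiguous sentence. The instruction to collect nothing more is attached expressly only to requested withdrawal, and the extending sentence could mean merely that the other groups may also be withdrawn. This is also a journal article, and the full protocol may separate stopping drug from leaving the study. The ambiguity is real. Still, the article is not silent here: it states a procedure and says to whom it extends, and the wording needs correcting even if no loss of data was intended.

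Other text might seem to rescue the score, but does not. The post-trial care section {30} requires follow-up after each treatment visit, but for support and reflection. The survival-data clause in {11b} does not cover MADRS.

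Several limits stand. The window is narrow. MADRS is called secondary in the Objectives and has no power calculation. Someone who refuses study procedures may refuse a MADRS as well, so the fix may recover little from that group.

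Three stronger readings are tempting, and the documents do not support them:

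- **Every removal ends data collection.** For adverse events and pregnancy no procedure is stated, so this is inference.
- **The MADRS comparison is biased in a known direction.** Because placebo was chosen partly to limit side effects, a reader might expect more adverse-event removals on psilocybin. The article gives no rates, so neither imbalance nor direction can be claimed.
- **Adverse-event follow-up is cut short.** The monitoring section {21a} has events followed through to resolution and makes no exception for removed participants.

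**Conclusion.** The point holds as a cheap improvement worth making. As written, {11b} most naturally ends data collection for participants removed for non-compliance or a new medical condition, whether or not they have withdrawn consent, and it is unclear for adverse events and pregnancy. The consequence is confined to the week-3 MADRS of people removed between Visit 1 and the week-3 visit. They are probably few, though that is a judgement, since no removal rate is given. Each one is 4% of an arm, and only an earlier observation would be left. The primary CBF contrast and the sample size are untouched. The verdict assumes that the extending sentence refers back to the procedure defined for requested withdrawal. The power range shown rests wholly on assumed inputs and is not an estimate for this trial.

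**What to change.** Amend {11b} in three respects:

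1. Limit the end of data collection to withdrawal of consent.
2. State that participants stopped by staff or the QI (adverse event, new condition, non-compliance, pregnancy) receive no further study drug but, unless they decline, complete the scheduled MADRS assessments, above all week 3.
3. State that the observed values are used in the intention-to-treat analysis, and that adverse-event follow-up to resolution under {21a} applies to these participants.

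The cost is a wording change to protocol and consent form, plus contacts that are already scheduled. These could be remote; the plan already does this at one week: "A second follow-up visit 1 week after the first treatment visit will be remote and will include relevant clinical scales". Payment is the existing $75 CAD per session.

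The downside is that usual treatment may have restarted before week 3: "Participants who have discontinued or completed their participation in the trial will be permitted to resume their usual standard-of-care". Some recovered scores would then reflect other antidepressant care. Record the date on which usual care resumed and flag those scores in reporting.
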